#### Analysis of secondary endpoints

– Endpoints 1 (change in child CPC score between Baseline, immediately after completion of the program, and 3 months after completion of the program) and 2 (change in parent PCL-5 scores). The analysis will be carried out in the same way as for the primary endpoint.– Endpoints 3 (relationship between different participant characteristics and pre-intervention CPC score) and 4 (relationship between different participant characteristics and response to treatment).The factors associated with the CPC score will be analyzed using multiple linear regression. Determinants of response to treatment (change in CPC score) will also be analyzed using multiple regression.

– Endpoint 5 (concordance between child and parent CPC scores).The concordance between the CPC score obtained by the child and that obtained by the parents will be analyzed at each measurement time using the intraclass correlation coefficient (ICC) and its 95% confidence interval.

– Endpoint 6 (concordance between child and parent CYRM scores).The concordance between the CYRM score obtained by the child and that obtained by the parents will be analyzed at each measurement time using the intraclass correlation coefficient (ICC) and its 95% confidence interval.

#### Sensitivity analysis

Sensitivity analyses will be carried out on the PP population to confirm the results obtained by the main analysis.

#### Exploratory analyses

### Observance

The number of performed sessions will be described. The discontinuation from the trial due to any cause (or due to specific causes) will be also reported and compared between groups.

Analyses for additional subgroups are not planned in the main study.

### Demographic and baseline characteristics

To ensure comparability, patient demographic and baseline characteristics will be summarized by group using descriptive statistics. For continuous variables, descriptive statistics (*n*, mean, standard deviation, standard error, median, minimum, and maximum) will be provided. For categorical variables, patient counts and percentages will be provided. Categories for missing data will be presented if necessary.

In the case of non-comparability for one or more parameters, an adjustment will be made on this/these parameter(s) for analysis of the judgment criteria. A multivariate linear regression model may be performed to account for potential confounders.

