**Methods:**

This study is a multicenter, evaluator-blinded RCT comparing CFTSI to supportive counseling. Eligible children (aged 7–17) must have experienced a TE within the past 45 days and exhibit at least one posttraumatic stress symptom. Exclusion criteria include severe cognitive impairment, ongoing abuse, or acute psychiatric emergencies.The CFTSI group will receive 5–8 structured, family-focused telehealth sessions targeting parent-child communication and coping. The control group will receive supportive counseling. The primary outcome is post-traumatic symptom reduction, assessed using the Child Posttraumatic Stress Checklist 3 months after completion of the program. Secondary outcomes include three-month symptom persistence, parental PTSD symptoms, and predictors of response. Analyses will use ANCOVA and regression models adjusted for baseline characteristics.

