### Randomization

At the inclusion visit, randomization will be conducted after verifying eligibility criteria and having obtained informed consent. The investigator will perform the randomization using the e-CRF system via Ennov Clinical^®^ software. Once the randomization is completed, the system will immediately generate the participant’s unique study identification number and assign them to either the control or experimental group. The site will then notify the investigator of the randomization result and group allocation.

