### Sample size

According to Hahn’s (2019) [15] meta-analysis, the effect size (Hedge’s g) in favor of the CFTSI intervention ranged from 0.86 to 1.17 (*N* = 640 children). In a Cochrane 2016 meta-analysis, comparing all psychotherapies versus control (short-term standard care), on total PTSD symptoms, the effect size is −0.53 (CI95%: −0.94; −0.12) when looking at family therapies [30].

Taking this effect size of −0.53 with a power of 80% and a two-sided alpha risk of 5%, it is necessary to include 57 patients per group (NQuery software). Given an expected drop-out rate of around 20%, it is necessary to include 70 patients per group, i.e. 140 patients in total.

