#### Analysis of primary endpoint

The analysis of the primary endpoint will be performed on an intention-to-treat basis. The primary endpoint (pre-post intervention variation in the child version of the CPC score) will be compared between the two groups using an analysis of covariance (ANCOVA) in order to adjust for the stratification criteria of the randomization. The effect size will be determined using Cohen’s d.

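### Beyond unnamed stratification criteria, covariates enter the endpoint models only if the arms are judged non-comparable at baseline, so the primary model is not fixed in advance

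*Protocol article*

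**What the plan says.** Four places in the protocol article bear on which covariates enter the endpoint models.

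- *Analysis of primary endpoint.* The endpoint is the "pre-post intervention variation in the child version of the CPC score", compared between arms "using an analysis of covariance (ANCOVA) in order to adjust for the stratification criteria of the randomization". Baseline CPC is not named as a covariate.
- *Analysis of secondary endpoints.* For change in child CPC and in parent PCL-5: "The analysis will be carried out in the same way as for the primary endpoint".
- *Randomization.* "The investigator will perform the randomization using the e-CRF system via Ennov Clinical". No stratification factor is mentioned here or anywhere else in the article.
- *Demographic and baseline characteristics.* After a descriptive baseline table comes the rule: "In the case of non-comparability for one or more parameters, an adjustment will be made on this/these parameter(s) for analysis of the judgment criteria". The next sentence adds: "A multivariate linear regression model may be performed to account for potential confounders".

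The abstract's methods paragraph puts no condition on adjustment: "Analyses will use ANCOVA and regression models adjusted for baseline characteristics".

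**The concern.** The rule applies to the endpoints without exception, so it reaches the primary analysis. It is not among the sensitivity analyses, which mention only the per-protocol population. It does not say what counts as non-comparable, which variables are eligible, or who decides.

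In a randomised trial a baseline difference between arms arises by chance. Its size says nothing about how strongly the variable predicts CPC, and predictive strength is what makes a covariate worth including. A rule driven by imbalance can bring in irrelevant variables and leave out a strongly prognostic one that looks balanced. The obvious candidate to be left out is baseline CPC, which is collected on every child.

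Two things are at stake. The primary model, and so the primary estimate and p-value, is not settled before the arms are compared. And the precision available from adjusting for baseline CPC is left to chance.

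**Working it through.** **The plan's own figure.** Inputs from *Sample size*: "Taking this effect size of −0.53 with a power of 80% and a two-sided alpha risk of 5%, it is necessary to include 57 patients", meaning in each arm. An exact two-sample t calculation gives power 0.801 at 57 per group and 0.794 at 56, so 57 is reproduced. The normal approximation gives 56. The checks below use 57 per arm and d = 0.53.

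**Assumptions, because the article gives no figures.** Non-comparable means baseline p<0.05. The pre-post correlation r of CPC is 0.3 or 0.5 (0.7 where shown). The baseline and follow-up SDs are equal, and 0.53 is in units of the follow-up SD.

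**Power by formula.** With effect e in units of the SD left in the model, power ≈ Φ(e·√(57/2) − 1.96), where √(57/2) = 5.339.

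- Change score without baseline CPC: SD = √(2(1−r)). At r = 0.3, SD = 1.183, e = 0.53/1.183 = 0.448, and power = Φ(2.391 − 1.96) = 0.67. At r = 0.5, SD = 1, e = 0.53, and power = Φ(2.830 − 1.96) = 0.81 (0.80 by exact t).
- Baseline CPC always in the model: SD = √(1−r²). At r = 0.3, SD = 0.954, e = 0.556, power = 0.84. At r = 0.5, SD = 0.866, e = 0.612, power = 0.90. With baseline CPC in the model, a change-score and a final-score outcome give the same treatment effect.
- Final score without baseline CPC: e = 0.53 and power about 0.80 whatever r is.

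**The conditional rule, by simulation.** Baseline CPC is added only when its baseline comparison gives p<0.05.

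| Base model | Never adjusted, r = 0.3/0.5 | Conditional rule | Always adjusted |
|---|---|---|---|
| Change score | 67/80% | about 68/81% | 84/90% |
| Final score | about 80/80% | about 81/82% | 84/90% |

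The rule moves power by about one point because, under randomisation, a p<0.05 trigger on one variable fires in about 5% of trials. In the rest baseline CPC stays out. A looser trigger would fire more often and recover more.

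**Type I error, rule strictly applied.** With the change-score model it is about 4.2 to 4.4%. A second simulation used a final-score model with eight independent baseline variables, one of them prognostic. It gave 4.7, 4.5 and 3.6% at r = 0.3, 0.5 and 0.7. Loosening the trigger to p<0.10 and p<0.20 at r = 0.5 gave about 4.3 and 4.0%. Fixed adjustment gave 5.0, 5.0 and 4.9%.

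**Type I error, worst-case discretion.** If the smaller of the adjusted and unadjusted p-values were kept, the final-score simulation gives 6.4, 7.5 and 8.2% at r = 0.3, 0.5 and 0.7. For a change score the figure is about 7 to 8%.

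**The case against.** The best defence is that a base model is stated, the rule only adds to it, and the statistical analysis plan may define non-comparability. Much of this stands.

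- *Adjustment is not wholly conditional.* A reader might infer that covariates enter solely through the imbalance rule. That is not so: the primary ANCOVA always adjusts for the stratification criteria. The weakness there is that they are never named.
- *The two sections do not contradict each other.* The rule extends the primary model, whose covariate list is not said to be exhaustive.
- *The rule does not cause the power gap.* The gap comes from leaving baseline CPC out of the base model, and deleting the rule alone would recover none of it. Whether it is left out can be disputed, given the term ANCOVA and the abstract's unconditional wording. The 68% also depends on 0.53 being standardised on the follow-up SD, which *Sample size* does not say.
- *False-positive inflation is not shown.* Strictly applied, the rule sits below 5%. The article describes no practice of choosing between p-values.
- *A high chance of a changed model is not a property of this plan.* Independent tests at 5% would flag at least one variable with probability 1 − 0.95^5 = 0.23 for 5 variables and 1 − 0.95^20 = 0.64 for 20. But the article announces descriptive statistics, with no baseline tests, threshold or number of variables.
- *Nothing says the decision is taken on unblinded outcomes.* Comparing baseline tables needs group labels, but not outcome data.
- *The optional regression* is permissive and can be read as supplementary, so it needs a label and need not be removed.

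The appeal to an unseen analysis plan does not remove the point. The article does more than leave a detail open: it commits to adjustment that depends on observed balance. An analysis plan that followed it would carry the flaw forward, and one that fixed the covariates would depart from it.

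**Conclusion.** The point holds in limited form. Apart from stratification criteria that are not identified, covariates reach the primary and secondary endpoint models only through an undefined judgement of baseline non-comparability, so the primary model is not fixed in advance.

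The measurable harm is modest. Strict use costs a little type I error (about 4 to 4.5% against 5% in the change-score setting) and leaves power roughly where an unadjusted analysis has it. What is forgone is the gain from fixed adjustment for baseline CPC. For a change score that gain is about 16 points at r = 0.3 (84 − 68) and 9 at r = 0.5 (90 − 81). For a final score it is about 3 (84 − 81) and 8 (90 − 82). Error rates above 5% arise only if the open criterion is used with discretion.

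These figures rest on the assumed p<0.05 trigger, the assumed correlations and the choice of base model. The conclusion that the rule is a poor way to choose covariates does not depend on them.

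**What to change.** Replace the non-comparability sentence with a covariate set fixed in advance: the baseline value of the outcome (CPC for the child endpoint, PCL-5 for the parent endpoint) plus any factors actually used to stratify the randomisation, named. State that these are used whatever balance is observed. Label any further adjusted model, including the optional multivariate regression, a sensitivity analysis. Keep the baseline table descriptive, as it already is, with no decision about the model attached to it. Align the primary-endpoint section and the abstract with the same list.

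The cost is wording only. Baseline CPC and PCL-5 are already collected at T0, and N does not change: with baseline CPC always in the model, 57 per group gives more than the planned 80% power at every correlation examined. The statistical analysis plan is due to be finalised before the last inclusion, so the list can be carried into it.

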### Handling of missing data

In the presence of missing data, the mechanism for the appearance of this data will be studied for each of the variables. If the MNAR (Missing Not At Random) hypothesis is rejected, the M.C.A.R. (Missing Completely At Random) versus MAR (Missing At Random) hypothesis will be tested, by studying the relationship between the status of the variable (missing data or not) and the values taken by the covariates. Under the hypothesis of a MAR or MCAR mechanism, i.e. that the probability of non-response for a variable is independent of the value taken by this variable, a multiple imputation method [31] will be implemented. Analyses will be carried out independently on each of the complete databases and their results will be taken into account in estimating the final parameters and their standard deviations. Finally, the concordance of the results obtained between the complete database and the database after imputation will be studied. The main analysis will be based on the database with imputation of missing data in order to be as close as possible to the ITT population. The analyses will be carried out at the Clinical and Epidemiological Research Unit of the Montpellier University Hospital. All statistical tests will be two-sided and the significance threshold will be set at 5%. All statistical analyses will be carried out using SAS enterprise guide or R.

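### Multiple imputation is made conditional on rejecting MNAR, which observed data cannot do, and the same section then imputes unconditionally

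*Protocol article*

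**What the plan says.** All statements are in the protocol article.

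- **Handling of missing data, gate.** The mechanism is to be examined variable by variable. The next step opens with "If the MNAR (Missing Not At Random) hypothesis is rejected"; MCAR is then tested against MAR "by studying the relationship between the status of the variable (missing data or not) and the values taken by the covariates".
- **Handling of missing data, definition.** Multiple imputation is to be used under MAR or MCAR, explained as "i.e. that the probability of non-response for a variable is independent of the value taken by this variable".
- **Handling of missing data, check.** After imputation, "the concordance of the results obtained between the complete database and the database after imputation will be studied".
- **Handling of missing data, main analysis.** "The main analysis will be based on the database with imputation of missing data", with the aim of staying close to the ITT population. No condition is attached.
- **Sensitivity analysis.** "Sensitivity analyses will be carried out on the PP population to confirm the results obtained by the main analysis".
- **Analysis of primary endpoint.** Intention to treat, with ANCOVA on the change in child CPC score.
- **Sample size.** Standardised effect 0.53 (given with a negative sign), 80% power, two-sided 5%, 57 per group, raised to 70 per group for dropout of around 20%.
- **Statistical methods.** Detail is left to an SAP, not shown here, to be finalised before the last inclusion.

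**The concern.** The section sets a decision rule for the primary analysis that nobody can carry out. It asks the analyst to reject MNAR, names no method for doing so, and does not say what follows if MNAR is not rejected. A later sentence in the same section imputes whatever the outcome of that step. Two analysts following the text in good faith could disagree on whether the primary analysis depends on a preliminary look at the data.

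Reporting is also at stake. If the step is treated as passed, the trial report may say that MNAR was ruled out, and no analysis of the observed data can support that. With around 20% dropout planned among recently traumatised families, readers will ask how far the result depends on the MAR assumption. The two checks in the article that might be offered as an answer do not address it.

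**Working it through.** **1. Can MNAR be rejected?** Let Y be the follow-up CPC score, X the observed data and R = 1 if Y is observed. The distribution of Y given X is a mixture:

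f(Y | X) = f(Y | X, R=1) · P(R=1 | X) + f(Y | X, R=0) · P(R=0 | X)

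The data inform f(Y | X, R=1) and P(R | X). They carry no information on f(Y | X, R=0). Setting it equal to f(Y | X, R=1) gives MAR; shifting it by any amount delta gives MNAR. Both choices fit the observed data identically, so no test can reject one in favour of the other without an assumption brought from outside.

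**2. What does the stated check do?** Relating missingness to covariates examines P(R | X). If it varies with X, that is evidence against MCAR. The check says nothing about f(Y | X, R=0).

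**3. Is the definition right?** MAR requires missingness to be independent of the unseen value given the observed data. The article omits the conditioning. Suppose dropout depends only on baseline CPC, and baseline CPC correlates with follow-up CPC. Dropout is then associated with follow-up CPC marginally, so the article's wording would exclude this case, although it is MAR and imputation using baseline CPC handles it.

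**4. Do the sentences agree?** The first imputes if MNAR is rejected and MAR or MCAR is accepted. The last imputes for the main analysis in every case. They cannot both govern the primary analysis.

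**5. Do the stated checks probe MAR?** Comparing complete-data with imputed results sets one analysis without imputation beside one that assumes MAR; neither lets the missing outcomes depart from MAR. The per-protocol analysis changes the population, not the assumption about missing outcomes.

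**6. Scale.** The plan's own figure first: a two-sample t-test with d = 0.53, two-sided 5% and 80% power gives 56.86, so 57 per group, as stated. With 70 per group and 20% loss, 70 × 0.8 = 56 are observed per arm, with power 79.4%.

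The shift in the between-group effect under a departure from MAR is

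shift = m_CFTSI × delta_CFTSI − m_control × delta_control

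where m is the missing share and delta is how much worse (in SD) missing outcomes are than MAR predicts. The deltas are assumptions; the documents give none. With the departure in the CFTSI arm only (at 20%, 14 of 70 children) and a MAR estimate of 0.53:

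| Missing share | delta 0.25 | delta 0.5 | delta 1.0 |
|---|---|---|---|
| 10% | 0.505 | 0.48 | 0.43 |
| 20% | 0.48 | 0.43 | 0.33 |
| 30% | 0.455 | 0.38 | 0.23 |

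At 20% missing, delta = 0.5 gives 0.20 × 0.5 = 0.10 SD, which is 0.10/0.53 = 19% of the planned effect; delta = 1.0 gives 0.20 SD, or 38%. If m and delta are equal in both arms, the shift is zero.

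Rough tipping point: SE ≈ √(2/56) = 0.189; critical difference ≈ 1.96 × 0.189 = 0.370; (0.53 − 0.370)/0.20 ≈ 0.8 SD. This ignores any precision gained from covariate adjustment and holds the SE fixed.

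**The case against.** The best defence is that the article commits to multiple imputation for the main analysis, and that imputation under assumed MAR is an accepted primary approach. This is correct. A reader might infer from the faulty gate that the main result has no valid missing-data basis, or that the ITT analysis collapses to complete cases because MNAR can never be rejected. The documents support neither: the main analysis is stated to be the imputed one, and no complete-case fallback is named.

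A second defence is that the article says the mechanism will be studied and speaks of testing only for MCAR against MAR. On that reading, rejecting MNAR could mean judging it implausible from recorded reasons. The article does require missing data to be justified (Data processing) and discontinuation causes to be reported by arm (Descriptive analysis). That softens the intent, but the text still presents the step as a hypothesis to be rejected, and a judgement of plausibility should be stated as an assumption.

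Third, details such as the imputation variables belong in the SAP, and the SAP may contain an analysis that departs from MAR. This stands: nothing here shows that the trial lacks one. The point is limited to what the article states, including a per-protocol analysis given the role of confirming the main result. The article does not define that population, so how many families it would drop is unknown.

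Fourth, dropout related to symptoms is not in itself MNAR. If it depends on CPC scores already measured, it is MAR. This also stands.

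**Conclusion.** The concern holds as an error in a stated rule. The gate asks for something observed data cannot deliver, lacks an alternative branch, rests on an incomplete definition of MAR and conflicts with the unconditional sentence later in the same section. The checks the article names cannot show whether the result survives a departure from MAR. The choice of multiple imputation itself is sound.

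The logical part needs no numerical assumption. The size does: the 19% and 38% reductions, and the tipping point near 0.8 SD, rest on 20% missing, a MAR estimate equal to the planned 0.53, and a departure in the CFTSI arm alone. They show why a sensitivity analysis is worth having; they do not predict bias in this trial.

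**What to change.** In the section on handling missing data, and in the SAP before it is finalised:

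1. Delete the step that requires MNAR to be rejected. Any comparison of missingness with covariates can stay as description, without deciding the analysis.
2. Define MAR as missingness independent of the unobserved value given the observed data.
3. State that the primary ITT analysis uses multiple imputation under an assumed MAR mechanism, unconditionally.
4. Add a delta-adjusted sensitivity analysis that shifts imputed outcomes over a prespecified range, allows the shift to differ by arm, and reports the tipping point.
5. Label the per-protocol analysis supplementary and drop the wording that it confirms the main result. The complete-versus-imputed comparison can remain as description.

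The cost is revised wording and a few extra imputation runs; no new data are needed. The downside is that the robustness statement may turn out less favourable.
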